### Sample size {14}

We conducted a power analysis using Optimal Design, a statistical simulation software which can estimate sample size for randomized controlled trials assessed using multi-level (i.e., mixed effects) models [74]. In Optimal Design, we estimated the required sample size for a person-randomized trial with six-time repeated measures (baseline, midpoint, post, 1-month follow-up, 3-month follow-up, 6-month follow-up, and 9-month follow-up). Additionally, for each outcome measure, we have four contrasts of primary interest (each intervention condition compared to the control), thus, using a conservative *p* value correction, we would divide the typical alpha value of .05 by four and get a *p* value threshold for significance of .0125. Finally, we assumed that we are interested in detecting a minimum post-treatment effect size of .3. We selected this value for the following reasons: 1) it is slightly lower than the effect sizes found in most previous trials of Shamiri, which range from .32–.83 at the latest follow-up points [3, 20, 33, 34], which will allow us to detect potentially smaller effects of the individual component interventions, and to detect effects in a universal sample, and 2) a standardized effects size of .3, which is considered small to medium, remains clinically meaningful and important in our view, whereas a change smaller than that may not be as clinically meaningful. Given these parameters, we found that a sample of 515 students would be needed to conduct a two-group trial with a power of .80. So, for this five-group trial, we multiplied that by 2.5, to get a final target sample size of 1288 students. Because in a past trial with 7-month follow-up there was a high dropout rate during follow-up of up to 40% [33], we will initially invite 2147 students to the sessions, assuming that around 40% of them will drop out prior to the sessions or during the follow-up period.

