Primary models will include all five groups, using the control group as the contrast group. Secondary models will include the four intervention conditions, using the full Shamiri intervention as the contrast group. Significant (*p* < .05 with a Holm-Bonferroni correction to account for four comparisons within each model) time × condition interactions will indicate that one condition produced significantly steeper improvements than another condition across the time included in the analyses. As described above and per recommendations outlined in past literature [78], the Holm-Bonferroni correction will be applied at a family-wise level (i.e., to account for multiple group comparisons on each outcome), rather than at a study-wise level.

Additionally, for all pairwise contrasts (including those comparing active interventions to each other) on all primary and secondary outcomes, effect sizes will be calculated as mean gain scores, to compare change within the various intervention and control groups.

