### Methods in analysis to handle protocol non-adherence and any statistical methods to handle missing data {20c}

Missing item and subject-level data will be imputed at least five times using Fully Conditional Specification (FCS), implemented using the multivariate imputation by chained equations (mice) package in R [79]. Multi-level models will be built using the pooled imputed datasets. Additionally, as appropriate, we may report results using the un-imputed dataset or conduct other sensitivity analyses using different styles of data imputation or using last observation carried forward. As described further under Strategies to Improve Adherence to Interventions, a selection of session recordings will be rated by independent raters for fidelity, and results of these ratings will be reported. If the study team or independent raters identify systematic deviations from the protocol by certain lay providers, students who received counseling from these lay providers may be removed from the dataset for sensitivity analyses.

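### A floor of five imputations is too low for the dropout this trial expects: an analysis run at that minimum could lose power and give verdicts that depend on the random seed

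*Protocol article*

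**What the plan says.** Section {20c} states that missing item-level and participant-level data "will be imputed at least five times" by fully conditional specification in the R package mice. It gives no rule tying the number to the amount of missing data, and no seed. It continues: "Multi-level models will be built using the pooled imputed datasets". An un-imputed analysis, other imputation styles and last observation carried forward are offered as options.

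Section {14} reports that in a past trial "there was a high dropout rate during follow-up of up to 40" per cent, and sets the number invited by "assuming that around 40% of them will drop out prior to the sessions or during the follow-up period".

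Section {20a} keeps every participant who consents, is randomized and completes baseline measures in all analyses. Anyone lost after that point is therefore imputed in the main analysis. The tests are time × condition interactions judged "with a Holm-Bonferroni correction to account for four comparisons within each model".

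**The concern.** The protocol chose to state a number, and five is the number it accepts. With m imputations the pooled estimate carries extra noise of B/m, where B is the between-imputation variance, and B is itself estimated on m − 1 degrees of freedom. When B is a sizeable share of the total variance and m is 5, the standard error is unstable and the reference t distribution has heavy tails. Both effects matter more at .0125 than at .05.

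Two things are at stake. The planned power of .80 may not be reached, although the data would support it. And an analyst repeating the same code on the same data with another seed may reach a different verdict on a primary contrast. That is a practical matter here, because section {31c} promises public code for published analyses and de-identified data on request.

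**Working it through.** **1. The plan's own figures.** Section {14} uses an effect of .3 SD, power .80 and 515 students for two groups, and for alpha "we would divide the typical alpha value of .05 by four", that is .05/4 = .0125. I take the test as two-sided.
- Noncentrality: .3 × √515 / 2 = 3.40. The critical value is 2.50, so power = Φ(3.40 − 2.50) ≈ .82. The noncentral t gives .815. This is close to .80; the variance components entered in Optimal Design are not given.
- 515 × 2.5 = 1287.5, rounded up to 1288.
- 1288 / (1 − .40) = 2146.7, rounded up to 2147.

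The 1288 is what should remain after the loss, so power of .80 with unlimited imputations is a natural starting point.

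**2. Fraction of missing information (FMI, λ).** The document does not give it, so I use .1 to .4. The top equals the dropout rate. To see where the trial may fall, I computed the information lost on a linear time × condition slope. Visits were at 0, 0.5, 1, 2, 4, 7 and 10 months, dropout was monotone, and the intraclass correlation was .4 to .6 (assumed), with or without a small random slope.
- 40% lost gradually by the last visit: λ about .31 to .35.
- All 40% lost from the 1-month follow-up onward: λ about .37 to .39.
- Only 20% lost gradually by the end: λ about .17.

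**3. Effect of m.** Scale the total variance at unlimited m to 1, so within-imputation variance is 1 − λ and B = λ.
- Relative efficiency at m = 5: 1/(1 + λ/5). For λ = .4 this is 1/1.08 = .926.
- Rubin degrees of freedom: about (m − 1)/λ² = 4/.16 = 25. The critical value at .0125 rises from 2.50 to 2.69.

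These formulas treat B as known. To include its sampling noise I simulated at least 200,000 datasets per setting:
- true noncentrality 2.498 + 0.842 = 3.339 (power .80 at unlimited m);
- pooled estimate with added variance λ/m;
- B drawn as λ·χ²(m − 1)/(m − 1);
- total variance T = (1 − λ) + (1 + 1/m)B;
- Barnard-Rubin degrees of freedom with complete-data df of 500 (assumed);
- two independent imputation sets per dataset.

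Results at alpha .0125 (power; share of datasets where two seeds disagree):

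| λ | m = 5 | m = 20 | m = 40 |
|---|---|---|---|
| .1 | .781; 6.3% | .794; 2.7% | .795; 1.9% |
| .2 | .750; 12.0% | .788; 4.4% | .794; 3.1% |
| .3 | .708; 18.2% | .781; 6.1% | .789; 4.1% |
| .4 | .663; 24.4% | .772; 7.9% | .785; 5.2% |

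Repeat runs, including complete-data df of 1000, moved power by no more than .005; the lowest cell ranged from .663 to .667. With m = 50, power is .786 to .798 and disagreement 1.7% to 4.6%.

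**4. Other conditions at m = 5.**
- Last Holm step (.05), λ = .4: power .719, disagreement 17.9%.
- Under the null at .0125: disagreement about 1% to 2%, with the rejection rate near nominal (.012 to .014).
- Stronger effects, λ = .2 to .4: disagreement about 6% to 16% if power at unlimited m is .95, and 2% to 8% if it is .99.

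**5. One dataset.** Suppose the p-value with unlimited imputations is .005 and λ = .4. With m = 5, 95% of seeds give p between .0003 and .092, and 54% fall below .0125. With m = 40 the range is .002 to .014, and 95% fall below.

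**The case against.** **Five is a floor.** Any larger number complies, and at m = 20 most of the problem is gone. This stands: the text does not show that the analysis will lose power, only that it permits an analysis that would.

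**Dropout is not the fraction of missing information.** Part of the 40% is expected before the sessions, and people who never complete baseline are not imputed. Grades come from school records for most who leave after the first session, so that primary outcome is less exposed. Results to the 1-month follow-up are to be analyzed before most of the follow-up loss. This also stands, and is why the range starts at .1. It does not make the top of the range unrealistic for the questionnaire outcomes over the full follow-up. Late visits carry much of the information on a slope, and step 2 gives .31 to .39 if 40% are lost after baseline.

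**The disagreement rates apply near the design effect.** True; they are small under the null and shrink for large effects.

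**Number and seed are analysis-plan detail.** Often so. Here the protocol states a number, and the point is that the stated number is too low.

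**Two stronger readings are not supported.** A reader might take the sentence on pooled datasets to mean that the imputed copies are stacked and analyzed as one. Nothing says so, and the usual mice workflow fits each dataset and pools the estimates. Stacking would also cause false positives, not lost power. A reader might also infer that last observation carried forward is the only sensitivity method named. Section {20c} also names the un-imputed dataset and other imputation styles, all optional.

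**Conclusion.** The point holds as a weakness in a stated minimum. At five imputations, power for a primary contrast could fall from .80 to between about .78 and .67, and two seeds could disagree on significance in about 6% to 24% of datasets. With 40 to 50 imputations the corresponding figures are about .80 to .79 and 2% to 5%.

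This rests on an assumed fraction of missing information of .1 to .4, a true effect giving .80 power with unlimited imputations, two-sided testing at .0125, and correct use of Rubin's rules. The largest losses belong to the questionnaire outcomes if dropout after baseline is near 40%. Under the null the seed matters little (about 1% to 2%), so this is not a concern about false positives. The pooling sentence needs clarifying but shows no error by itself.

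**What to change.** In section {20c}, replace the minimum of five with: the number of imputations will be at least the percentage of incomplete cases (about 40 to 50 under the expected dropout), with the random seed recorded and reported.

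In the same edit, reword the pooling sentence to say that the multi-level model is fitted in each imputed dataset and the estimates are combined by Rubin's rules. This is a clarification only.

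A delta-adjusted imputation, to probe departures from missing at random, could be added in the same code but is optional.

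The cost is two sentences and some computing time; no new data are needed.

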### Plans to give access to the full protocol, participant-level data, and statistical code {31c}

The authors plan to grant full public access to the trial protocols and training materials, to participant-level data upon request once it is fully de-identified and cleaned, and to statistical code for published analyses.

## Oversight and monitoring

### Composition of the coordinating center and trial steering committee {5d}

The coordinating center is located at the Shamiri Institute headquarters in Kiambu, Kenya (near Nairobi), a secure, locked building with secure, locked rooms inside of which the study team may safely store data. The trial steering committee consists of the study PIs (both PhD-level mental health clinicians), two doctoral students in clinical psychology, and an affiliate of Shamiri Institute with a bachelor’s in psychology. Approximately half of the trial steering committee is located in Kenya, while the other half is located in the USA. All members of the trial steering committee meet weekly to plan and manage the trial and discuss any issues that may arise; they will continue to meet weekly or bi-weekly when the study is implemented, and follow-up data collected. The trial steering committee oversees data management including collection and entry of data, plans day-to-day trial implementation and supervision for lay providers, oversees participant recruitment and consulting, and reviews and addresses safety events as they occur.

### Composition of the data monitoring committee, its role and reporting structure {21a}

The Data Monitoring Committee will meet with the study investigators once yearly to review trial progress and aggregate findings, as well as to review non-identifying reports of any adverse events and steps taken by the study team to address them. They will then provide their guidance about any further next steps that might help protect participant safety and wellbeing, and will opine as to whether adverse events were related to or independent from the trial. The Data Monitoring Committee may also be contacted outside of these yearly meetings if the investigators feel they would benefit from their input. The Data Monitoring Committee will be composed of several individuals who are uninvolved with the study but have expertise in youth mental health care in sub-Saharan Africa. Notably, these individuals will not receive any royalties from the Shamiri Institute or from the Templeton World Charity Foundation for their work. Thus, they will have no competing interests.

### Adverse event reporting and harms {22}

The emergency protocol for participant risk scenarios was developed using the American Academy of Pediatrics guidelines for child and adolescent suicide risk, which encourage explicitly asking about suicidal thoughts, intent, plans, and history, as well as assessing risk and protective factors and triangulating interview findings with symptom measures [80]. These guidelines also suggest employing sensitivity and having a natural conversation about how the youth is feeling, as opposed to simply firing off a series of questions about suicide risk [80]. Additionally, guidelines from the American Academy of Child and Adolescent Psychiatry suggest balancing participant confidentiality and comfort with the need to inform guardians (i.e., teachers in the case of this present study) of child or adolescent risk. In all cases in which harm may be imminent (i.e., high risk), it is necessary to inform the guardian of youth risk [80, 81]. However, in cases in which the harm is not intended or imminent, steps are less clear-cut and must involve balancing participant comfort and confidentiality with safety, where safety is most important [81]**.** In an effort to achieve the appropriate balance, we will inform school staff of students who study staff identify as currently at a medium or high risk of suicide; we will not routinely inform schools of low-risk cases, but our expert clinician will consider that step in low-risk cases if it seems appropriate. In all low-risk cases, study staff will continue monitoring and evaluation conversations weekly and inform the school if the student rises to a higher risk level. Those with medium risk or higher will be very strongly encouraged to seek professional help, facilitated by the study team and in coordination with guardians. Additionally, all cases of risk or other adverse events will be reported to the IRB of record, the KU IRB, and we will follow their guidance in addressing these events.

The study staff (including lay providers) will not systematically ask participants about risk in any questionnaires or in the group meetings. This is to avoid unnecessary stigma and discomfort. However, in the event that a student displays potentially serious mental health concerns (e.g., if a participant mentions thoughts of/desire to harm self or others) or other concerns that especially concern or overwhelm the lay provider, the lay providers will be trained to follow-up with the student privately and promptly (e.g., right after the group session) to further assess the situation—for example, by asking about thoughts of harm, and whatever other concerns the student has mentioned. Afterward, group leaders will be trained to promptly speak with their supervisor. The supervisor will then assist with triage (by asking about thoughts of harm, and, depending on the response, methods, plans, intent, and history). If appropriate and consistent with school policy, the supervisor will organize follow-up and referral to appropriate resources. All such conversations, even those that yield a designation of “no risk,” will be reported immediately to study staff, and all conversations that yield a risk designation of medium risk or higher will result in an immediate phone conversation with the local study PI, an experienced clinician. See emergency protocol in supplementary materials for more details.

If less urgent problems are uncovered in the risk assessment or elsewhere (e.g., academic troubles), we may, after consultation with the PIs and expert clinicians involved in the study, refer these students to the appropriate school administrator (e.g., school chaplain, school counselor, school principal). In these cases, we will follow the standard referral procedures used by these schools. For cases in which the study PIs disagree with each other or would like a third opinion about the need to consult the administration or about other potential steps, we will contact the Kenyatta University IRB to inquire about an appropriate path forward.

### Frequency and plans for auditing trial conduct {23}

For this trial, especially because the study procedures are very unlikely to have adverse effects on participants, we do not have plans for auditing apart from that described above done by the Data Monitoring Committee and any updates requested by the IRB of record or by the trial sponsor, the Templeton World Charity Foundation. If the investigators, sponsor, or IRB become concerned about any aspect of trial conduct, the study team will consider bringing in an independent auditor to help diagnose and resolve trial conduct issues.

### Plans for communicating important protocol amendments to relevant parties (e.g., trial participants, ethical committees) {25}

Any changes to trial protocols will be communicated first to the investigators through email, phone, or video conference in routine meetings, and then, when the investigators judge it appropriate, to the IRB of record (Kenyatta University IRB) via email, to the trial sponsor via email, and on the public, online PACTR trial registration page. When deemed necessary by the investigators or the IRB, trial participants will be notified about protocol changes via announcements at their schools.

### Dissemination plans {31a}

The authors plan to disseminate findings of this trial through manuscripts published in peer-reviewed journals, through data, manuscript, and code sharing on open access platforms such as OSF, and through presentations at academic conferences. Reporting of these results will be broken into several articles because of the large number of outcomes, groups, timepoints, and questions of interest in this study, and the limited word counts at almost all academic journals. Additionally, to the extent possible, the authors plan to disseminate intervention protocols and online versions of the intervention publicly online, and to publish results in popular media outlets. The authors will strive to make all published materials open access.

## Discussion

Here, we described the design of a comparative effectiveness randomized controlled trial designed to evaluate four school-based mental health promotion interventions delivered by lay counselors. Through this study, we will understand if the interventions produce an effect on depressive symptoms, anxiety symptoms, academic performance, and subjective wellbeing. We also aim to identify for whom these interventions are most effective, their mechanisms of change, and their potential impacts on secondary outcomes.

The results from this study will be used to inform future efforts (by our group and potentially others) to identify and disseminate the most effective, cost-effective, and culturally appropriate ways to promote mental health among Kenyan adolescents. This work will directly inform our efforts through the Shamiri Institute (https://www.shamiri.institute/), a non-profit organization that forms partnerships with community organizations in Kenya to implement evidence-based mental health and wellness interventions. The knowledge acquired from this trial (e.g., which character strength intervention(s) are most effective? For whom do these interventions have the strongest effect?) will directly inform our group’s efforts to continue to disseminate mental health interventions throughout Kenya. The knowledge and materials produced through this trial may also inspire and inform mental health promotion efforts in other LMICs, and even in high-income countries such as the USA, where it is estimated that only a third of youth in need of mental health care receive it [82].

The trial’s results should be interpreted in light of some scientific and practical limitations. First, we are testing these interventions as universal interventions, in which students are eligible to participate regardless of their level of symptoms. While there are advantages of this approach such as not requiring pre-screening and, likely, reducing stigma for participants, our findings may not generalize to targeted interventions, in which all group members meet a certain symptom threshold. Second, it is possible that training group leaders in the single-component interventions (gratitude, growth, and values) also improves their ability to perform the combined Shamiri intervention. While we will be able to measure group leaders’ fidelity to each of the interventions, it is possible that the nature of our trial (and training) could provide group leaders with more competence in delivering the combined intervention. Third, when performing studies in schools (and other naturalistic settings), researchers often have less control over the setting. As a result, there may be certain threats to internal validity (e.g., students sharing information about their group with other students, academic schedules requiring delays in the collection of data). In our view, these threats to internal validity are counterbalanced by benefits to external validity [83]. Furthermore, to promote the successful implementation of our study, our group will apply best practices we have learned through our previous work [84].

Future research will be needed to identify additional ways to promote mental health in LMICs. For example, future research could compare the effectiveness of character strength interventions (such as Shamiri) to traditional interventions like cognitive behavioral therapy. Previous studies have found that cognitive behavioral therapy and behavioral activation can be effective treatments for youths in LMICs [85, 86]. However, little is known about how these interventions compare to Shamiri or other character strength interventions. Another promising avenue for future research is the development and evaluation of remotely delivered mental health interventions, such as digital interventions, for youths in LMICs. Digital and other remote mental health interventions may be especially valuable in LMICs, given their widespread availability, low costs, and growing evidence base [87–91]. Although much of the evidence on digital mental health interventions for youths come from high-income countries, early efforts are already underway to adapt and evaluate online and smartphone-based self-help interventions in LMICs (e.g., [22, 92, 93]). Additionally, future research is needed to understand how to effectively develop and implement stepped-care systems in LMICs [94, 95]. Stepped-care systems may be especially useful in LMICs, where resources for mental health care are generally scarce and access to mental health care is highly limited. Such work could be guided by efforts to understand “what works for whom.” Understanding which youths benefit from low-intensity services, and which youths require higher-intensity services, could inform how stakeholders allocate individuals to different interventions.

Ultimately, a variety of efforts will be needed to expand access to evidence-based mental health care worldwide. It is our hope that our trial will be one of many efforts toward promoting youth mental health care worldwide.

